### Results of randomisation

The final choice of restriction criteria resulted in 1598 acceptable allocations from which one was randomly chosen. Table 2 and **Error! Reference source not found.** summarise the allocation process.

6 clinics (clusters) have been allocated to each study arm in the Nangahar stratum, and 5 per arm in Kunduz stratum. Study arm 0 denotes no RDT, and study arm 1 denotes RDT (intervention) – see next section.

Table 2: Results of intervention allocation process

| **Kunduz** | | |  | **Nangahar** | | |
| --- | --- | --- | --- | --- | --- | --- |
| **Cluster** | **Clinic** | **Study arm** |  | **Cluster** | **Clinic** | **Study arm** |
| 1 | Ajighan | 0 |  | 11 | Baro | 0 |
| 2 | AngorBagh | 0 |  | 12 | Batikot | 1 |
| 3 | ArbabRamazani | 0 |  | 13 | Behsood | 0 |
| 4 | BolaQachi | 1 |  | 14 | Chardhi | 1 |
| 5 | CharSari | 1 |  | 15 | GardiGhos | 1 |
| 6 | Khan Abad | 1 |  | 16 | Khewa | 0 |
| 7 | KhwajaGhaltan | 0 |  | 17 | LandaBuch | 0 |
| 8 | Madrasa | 1 |  | 18 | MamandDara | 1 |
| 9 | Nick Pay | 1 |  | 19 | NajmulQura | 1 |
| 10 | SandoqSai | 0 |  | 20 | Rodat | 0 |
|  |  |  |  | 21 | SangarSarai | 1 |
|  |  |  |  | 22 | Shegay | 0 |

Table 3: Summary of clusters allocated to study arms in Phase 1

| **Arm 0 (no RDT)** | **Arm 2 (RDT)** |
| --- | --- |
| Ajighan | Batikot |
| AngorBagh | BolaQachi |
| ArbabRamazani | Chardhi |
| Baro | CharSari |
| Behsood | GardiGhos |
| Khewa | Khan Abad |
| KhwajaGhaltan | Madrasa |
| LandaBuch | MamandDara |
| Rodat | NajmulQura |
| SandoqSai | Nick Pay |
| Shegay | SangarSarai |

### Baseline characteristics by study arm

It can be seen from **Table 4** that given the above restricted randomisation we achieved a suitable balance on those factors included in the randomisation. A baseline table showing all individual and cluster-level covariates would also be interesting to include in a paper to examine the balance on factors not included in the randomisation.

**Table 4: Examining the balance after randomisation**

|  | **No RDT (n=11)** | **RDT (n=11)** |
| --- | --- | --- |
| Total sample size | 1280 | 1262 |
|  |  |  |
| Harmonic mean number of patients per cluster | 66.03 | 69.28 |
|  |  |  |
| Number of health posts | 111 | 109 |

### Validation matrix

To assess the validity of the design for the combination of thresholds a matrix was made. The columns and rows of the validation matrix represent each of the 22 clusters. The elements of this matrix are the proportion of times each pair of clusters is allocated to the same group in the 1598 acceptable allocations i.e. the probability that the ith cluster is being allocated to the same intervention group as the jth cluster. The matrix was then examined for under- and over-represented pairs that would highlight any potential causes for concern in the randomisation.

The validation matrix for the final choice of restriction criteria showed that, with the exception of two pairs (3,14) and (9,20), the matrix elements range from 20% to 70% indicating under- and over-representation of a few clusters but the majority were around 50% illustrating a valid randomisation. Inspection of the data showed no obvious reasons for the two pairs (3,14) and (9,20) only being together in 0.1% of the allocations, and could not be increased by loosening the thresholds. However, despite this there are still 159 possible allocations in which these two pairs of clusters can be allocated to the same study arm; hence it was concluded that this restriction criteria was valid.

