### Randomisation Methods:

### Number of unrestricted allocations

The study is a stratified cluster randomised trial with a total of 22 clusters.

In Kunduz the total number of ways of allocating the 10 clusters to the two intervention groups, assuming equal number of clusters per arm:

$$\binom{10}{5}\binom{5}{5}=252$$

In Nangahar the total number of ways of allocating the 12 clusters to the two intervention groups, assuming equal number of clusters per arm

$$\binom{12}{6}\binom{6}{6}=924$$

Therefore in total there are: 252 x 924 = 232,848 possible allocations of 22 clusters into the 2 study arms after stratification.

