### Exploring combinations of thresholds

Combinations of thresholds were examined and the final choice was based on achieving acceptable balance between the study arms and maintaining an unbiased and valid design. As described by Moulton (2004) a design is biased if there is any difference across the clusters in their probability of allocation to any given treatment. A randomised design is said to be valid if every pair of clusters has the same probability of being allocated to the same treatment. An unbiased design is unlikely to occur in practice but the validity is more questionable when conducting a constrained, or restricted, randomisation. If the design is not valid there is a risk that the Type I error changes from its nominal value of 0.05.

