### Final combination of balance criteria

The final choice included the following restrictions:

1. Total sample size per arm differing by no more than 50
2. Harmonic mean in each cluster being within the range 65 to 71
3. The number of health posts per arm differing by no more than 10 health posts

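### The restricted randomisation is called valid on a count of 159 allocations that contradicts the stated 0.1% of 1,598, when at most 38 are possible

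*Protocol*

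**What the plan says.** Section 2.5.4 starts from "252 x 924 = 232,848 possible allocations of 22 clusters into the 2 study arms after stratification". Three restrictions follow under Final combination of balance criteria: "Total sample size per arm differing by no more than 50"; "Harmonic mean in each cluster being within the range 65 to 71"; and "The number of health posts per arm differing by no more than 10 health posts". The second is worded per cluster, but section 2.5.3 and Table 4 show that it applies to each arm. Section 2.5.5 reports the result: "The final choice of restriction criteria resulted in 1598 acceptable allocations from which one was randomly chosen".

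Section 2.5.4 defines a valid design as one in which every pair of clusters has the same probability of sharing a treatment, and gives the reason for caring: "If the design is not valid there is a risk that the Type I error changes from its nominal value of 0.05".

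The Validation matrix text takes its proportions over the 1,598 accepted allocations. All pairs but two lie between 20% and 70%. The exceptions, (3,14) and (9,20), are described as "only being together in 0.1% of the allocations, and could not be increased by loosening the thresholds", with no evident cause found in the data. The text then concludes that the criteria are valid, on the ground that "there are still 159 possible allocations in which these two pairs of clusters can be allocated to the same study arm".

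**The concern.** The count of 159 carries the argument. The pair matrix flagged two pairs as almost never together, and the count is what the protocol uses to set that warning aside. It does not agree with the percentage in the sentence before it. If the percentage is right, the two pairs are in effect always assigned to opposite arms, and the design fails the protocol's own definition of validity.

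The two supporting statements, that no cause is apparent and that looser thresholds do not help, would also leave the team unaware of what produced the pattern. Section 2.5.1 says Phase II will be allocated by the same methods, so the text may be relied on a second time.

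**Working it through.** **The stated figures.** 0.001 × 1,598 = 1.6, or about 2 allocations (2/1,598 = 0.125%). 159/1,598 = 9.95%. Since 0.1 × 1,598 = 159.8, the count may come from reading 0.1 as a proportion rather than a percentage. That explanation is an inference; the conflict is not.

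**Parity.** All three criteria treat the arms symmetrically, so swapping the arms of an accepted allocation gives another accepted allocation in which the same pairs are together. Any such count must be even, and 159 is odd.

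**Enumeration.** Inputs are the 22 Phase I quotas weighted for a harmonic mean of 68 (table in section 2.8.3, sum 2,542), split 5:5 in Kunduz and 6:6 in Nangarhar: 252 × 924 = 232,848 allocations.

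The run reproduces the protocol's own figures first:
- Table 1, total size difference ≤50: 0.119. The other seven size rows also agree.
- Table 1, harmonic-mean ranges from 67-69 to 63-73: 0.032, 0.085, 0.141, 0.196, 0.250.
- Table 4, drawn allocation: sizes 1,280 and 1,262; harmonic means 66.03 and 69.28.

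With size difference ≤50 and both arms' harmonic means inside the range:

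| Harmonic-mean range | Accepted | (3,14) together | (9,20) together |
|---|---|---|---|
| 66-70 | 3,220 | 0 | 0 |
| 65-71 (chosen) | 5,826 | 38 (0.65%) | 38 (0.65%) |
| 64-72 | 7,882 | 578 (7.3%) | 578 (7.3%) |
| 63-73 | 9,436 | 1,272 (13.5%) | 1,256 (13.3%) |

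At 65-71 the same 38 allocations keep both pairs together, so the count is 38 whether one reads it as both pairs or either pair. Adding the health-post criterion can only remove allocations. The ceiling is therefore 38, or 38/1,598 = 2.4%, and 159 cannot occur.

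**Why these pairs.** The quotas are 25 (cluster 3, ArbabRamazani), 36 (14, Chardhi), 20 (9, Nick Pay) and 20 (20, Rodat), the four smallest of the 22. An arm's harmonic mean is 11 divided by its sum of reciprocal quotas. All 22 reciprocals sum to 22/67.617 = 0.3254. These four give 0.0400 + 0.0278 + 0.0500 + 0.0500 = 0.1678, just over half.

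A harmonic mean of at least 65 caps each arm's sum at 11/65 = 0.1692. The other arm then has at least 0.3254 − 0.1692 = 0.1562, so the arms may differ by at most about 0.013. Putting 9 and 20 in one arm and 3 and 14 in the other gives a difference of 0.1000 − 0.0678 = 0.032, which the other 18 clinics can seldom offset while the totals stay within 50.

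**The allocation drawn.** In Table 3, ArbabRamazani and Rodat are in the no-RDT arm, and Chardhi and Nick Pay in the RDT arm. Both pairs are split.

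**The case against.** Several points on the other side stand.

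- **The draw met its criteria.** Table 4 confirms size and harmonic mean, and reports 111 and 109 health posts. Separating very small clinics is also part of what balancing intends.
- **A reader might infer that Type I error is inflated.** The documents do not show this. By mirror symmetry every clinic still has a 50% chance of each arm. A simulated province-adjusted cluster-level t-test, assuming normal cluster effects, gave mean rejection of 5.0-5.1% when outcome was unrelated to clinic size and 2.7-2.9% when it moderately tracked log size. For a single fixed outcome pattern the rate ranged roughly from 1% to 10%. Not assured is a fair description; inflated is not.
- **A reader might infer that loosening cures the problem.** The widest harmonic-mean range in Table 1, 63-73, still leaves both pairs near 13%, below the 20-70% band. The claim that the share could not be raised is wrong, but no tabulated range restores the band.
- **A reader might carry the pair result into Phase II.** Section 2.5.6 re-randomises within each Phase I arm, and the target harmonic mean becomes 182. The result does not transfer without a new check.
- **The 1,598 itself cannot be reproduced.** The listed health posts sum to 207, while Table 4 sums to 111 + 109 = 220; with the listed counts the three criteria give 1,958. Shares that depend on health posts are therefore insecure and are not used here. The ceiling of 38 does not depend on them.

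The protocol also leaves the analysis to a later plan, so the permutation test proposed below is a recommendation for that plan rather than an omission from this document.

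**Conclusion.** The point holds. The count of 159 is wrong: it contradicts the adjacent 0.1%, it is odd where only even counts can arise, and it exceeds the ceiling of 38. The statements about cause and about loosening also fail on the protocol's own quotas. What is left is a design in which two pairs are in effect always split, so the stated ground for calling it valid falls away and, by section 2.5.4, the nominal 5% error is not assured.

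This rests on the rounded Phase I quotas in section 2.8.3, which reproduce Table 1, and on reading the harmonic-mean rule per arm. Applying that rule to one arm only gives 95. Unrounded quotas give 100, but do not reproduce Table 1. Both are below 159. It does not show that the Phase I allocation is biased or must be redrawn. The correction should be made, but it is mainly one of text and supporting analysis.

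**What to change.** **Text, section 2.5.5.** Replace 159 with the true count from the stored enumeration. Withdraw the statements that no cause is apparent, that the share could not be raised, and that the criteria are therefore valid. State that the two pairs are in effect always split because they hold the four smallest quotas, and that the nominal 5% level is not assured as a result.

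**Phase I analysis.** Base the primary p-value, or at least a confirmatory one, on a permutation test over the list of accepted allocations. That test is exact under this restricted draw. It needs the 1,598 allocations to be kept, or regenerated with the health-post counts actually used.

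**Phase II.** Drop the harmonic-mean restriction, or reset its range around 182. The Phase I range cannot be reused: the overall Phase II harmonic mean of 182.19 must lie between the two arm values, so 65-71 would accept nothing. Re-run the pair matrix for re-randomisation within Phase I arms before drawing.

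**Cost.** A text edit, a short permutation script and a re-run of the existing R enumeration. The drawback is less equal harmonic means in Phase II. As a guide to the precision at stake, the variance factor (1 + (m−1)×ICC)/m at the protocol's ICC of 0.5 is 20.5/40 = 0.5125 for m = 40 and 34.5/68 = 0.5074 for m = 68, a difference of 1%. This depends on the ICC: at an assumed 0.05 the factors are 2.95/40 = 0.0738 and 4.35/68 = 0.0640, about 15% apart.

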### Trial Profile:

**Figure: Trial schematic for Phase 1.**

If the criteria for running phase 2 of the trial are met the 22 clinics will be re-randomised so that 50% of those clinics in arm 1 are randomised to arm 3 and 50% to arm 2, and 50% of those in arm 2 will be randomised to arm 3 with 50% remaining in arm 2 (figure 2).

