### Trial Arms:

**Phase I:**

*Arm 1: Non-intervention arm:*

The non-intervention arm will be based on the existing clinical diagnosis, pre-referral treatment and referral to a clinic in areas where RDTs have not been deployed at CHW level. Arm 1 CHWs will receive refresher training according to the National Strategy for CBMM which includes the current IMCI guidelines.

Vs:

*Arm 2: RDT Arm*

Provision of community level diagnostics by rolling out RDTs to CHWs through the national strategy for Community based Management of Malaria. The arm has been designed exactly as the current National guidelines for RDT implementation..The arm will include:

- Clinic level microscopy or RDT and CHWs using RDTs to provide parasitological diagnosis to diagnose, treat and/or refer patients. Under this scheme, CHWs will be provided with CQ, SP and artesunate (AS). Depending on the diagnostic result, they prescribe according to the National Treatment Guidelines (CQ for confirmed vivax, SP and AS for confirmed falciparum, and no antimalarial for a negative result).
- CHW training will be conducted exactly as described in the CBMM strategy, using a “trickle down approach” where Training of Trainers takes place at the central level for provincial trainers of local NGOS who run the health service. These, in turn, run workshops for training CHSs and CHWs (see section 2.2 for pre-evaluation of training and roll-out). Participants will receive training to enforce revised IMCI guidelines, taken from the CBMM strategy document, which include an RDT in the algorithm for fever (see annex 2).
- There are no plans for additional support or refresher training, and no plans for quality control and assurance contained in the National Plan.
- CHWs are not equipped with suitable storage facilities for the RDTs, for example evaporative coolers.
- Monitoring and evaluation takes place according to the draft strategy.

The second phase of the trial will be initiated in Feb 2012. The second phase of the trial will re-randomise clinics to either the RDT arm (as in arm 2, above) and a third arm (arm 3). The third arm will answer the question: “how can the performance of RDTs at community level be enhanced?”. The same set of outcomes will be used to measure the relative effectiveness of each approach. A revised random allocation using the same methods will be conducted for the Phase II randomisation.

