**Curriculum for CHS and CHW training:**

| **Training Topic** | **Contents** | **Registrars** | **Arm 1** | **Arm 2** | **Arm 3** |
| --- | --- | --- | --- | --- | --- |
|  |  |  |  |  |  |
| *Trial Procedures* | 2 day | Trainer: Conducted by ACTc senior researchers | | | |
| Introductory training | Objectives and overview of the study – tone is not on treatment accuracy, but on different methods for diagnosis and treatment of illness at community level |  | **√** | **√** | **√** |
| Form Filling | Introduction to the form – what information is collected  Each section of the form  How to fill the form (ticking boxes)  Making corrections of mistakes  Practice using a series of case studies | **√** | **√** | **√** | **√** |
| Specimen Collection | Blood and sharps safety  Taking a blood spot  Storing the blood spot in package | **√** | **√** | **√** | **√** |
| Package training / equipment provided | Package contents  Patient numbers  Process for enrolling patients – consent forms  Handing the package to the registrar | **√** | **√** | **√** | **√** |
| Ethics and Consent | Basic Ethics – human use in research.  Consent – what is it? How to get it? | **√** | **√** | **√** | **√** |
| Fraud and bogus data collection | What happens?  How do we detect it? | **√** | **√** | **√** | **√** |
| Basic SoP for field data collection | Run through the CHW SoP for recruitment | **√** | **√** | **√** | **√** |
| Advanced Training in trial SoP | Covers all sections from Registrar and below | **√** |  |  |  |
| *Intervention Training* |  |  |  |  |  |
| *Length and Trainers* | 2 days for clinics in intervention arms | Trainers: Master trainers – from NGOs and MRC staff; [name] (HealthNet malaria master trainer, JAA) and [name] (HealthNet malaria master trainer, KDZ). Master trainers will train CHSs who will train CHWs in the intervention arm 1. | | | |
| Refresher Training of ToT |  | For Master Trainers in Arm 1 | | | |
| RDT Training* | Copied from the CBMM and any other training documents developed by NMLCP and partners |  | **√ -** possibly without RDT | **√** | - |
| RDT+ Training | Identified by ACTc team and added for phase II |  | - |  | **√** |

* Master trainers trained by NMLCP; Master trainers CHWs (in their own clinics).

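### The Phase II split within each Phase I arm is not delivered by the randomisation method named for it, and the pooled Arm 3 versus Arm 2 contrast averages two different training comparisons

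*Protocol*

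**What the plan says.** Section 2.5.6 (Trial Profile) sets the Phase II allocation separately for each Phase I arm. For the former control clinics it reads: "50% of those clinics in arm 1 are randomised to arm 3 and 50% to arm 2". The former RDT clinics are divided likewise, one half moving to the extended programme and the other staying where it is.

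Section 2.5.1 (Trial Arms) describes the procedure differently: "A revised random allocation using the same methods will be conducted for the Phase II randomisation". Those methods are in section 2.5.4. The trial is described there as stratified, "The study is a stratified cluster randomised trial with a total of 22 clusters", and the strata used in the count are the two provinces. The three final restrictions concern arm size: "Total sample size per arm differing by no more than 50", a harmonic mean between 65 and 71, and at most 10 health posts' difference. Phase I arm is neither a stratum nor a restriction.

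Section 2.5.5 gives the Phase I result: "6 clinics (clusters) have been allocated to each study arm in the Nangahar stratum, and 5 per arm in Kunduz stratum".

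On training, section 2.5.1 says of the RDT arm: "There are no plans for additional support or refresher training". The curriculum table in section 3.3 describes the Arm 3 module as "Identified by ACTc team and added for phase II".

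**The concern.** One section makes the Phase II allocation depend on Phase I arm; the other names a procedure that does not. Whoever runs the Phase II randomisation could follow section 2.5.4 and obtain a list that breaks section 2.5.6. Phase I arm is a plausible correlate of Phase II performance, since section 2.8.1 expects 10% versus 50% correct treatment in Phase I. If former RDT clinics fall unevenly between Arms 2 and 3, carry-over from Phase I enters the Arm 3 effect, in either direction.

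The second issue remains even with good balance. Among former control clinics, health workers in both Phase II arms receive RDT training for the first time. Among former RDT clinics, those in Arm 2 appear to stay on their Phase I training, because no refresher is planned, while those in Arm 3 are trained again. The pooled contrast therefore averages package against standard rollout, both new, with package plus retraining against standard rollout some months old. Phase II asks how community RDT performance can be enhanced, and these two comparisons need not give the same answer.

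**Working it through.** **Inputs.** Province and Phase I arm of each clinic: Table 2 (section 2.5.5). Phase I and Phase II cluster quotas: section 2.8.3. Health posts per clinic: section 2.8.2. Restrictions: section 2.5.4. Planned Phase II difference of 20 points: section 2.8.1. The effect of Phase I RDT experience on Phase II performance is not given; I assume 5 to 20 points.

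**Reproducing the plan's figures.** C(10,5) × C(12,6) = 252 × 924 = 232,848, as stated. The Table 2 allocation with the section 2.8.3 quotas gives totals of 1280 and 1262 and harmonic means of 66.03 and 69.28, matching Table 4. The stated 1598 acceptable allocations do not reproduce: I obtain 1,958. The listed health posts sum to 102 and 105 per arm, whereas Table 4 shows 111 and 109. Results that use the restrictions are therefore approximate.

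**Exact half.** 11 / 2 = 5.5 overall and 5 / 2 = 2.5 in Kunduz; 6 / 2 = 3 in Nangarhar. Rounding to 5:6 in one Phase I arm and 6:5 in the other keeps 11 clinics in each Phase II arm.

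**Section 2.5.4 methods without section 2.5.6.** I enumerated all 232,848 allocations and counted former RDT clinics in Arm 3. For the third row, the limits were scaled to Phase II: 50 × 6792/2542 ≈ 134; 65 × 182/68 ≈ 174; 71 × 182/68 ≈ 190; health posts unchanged at 10.

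| Method | Accepted | 5:6 or 6:5 | 4:7 or worse | 3:8 or worse |
|---|---|---|---|---|
| Province strata only | 232,848 | 138,124 | 94,724 (40.7%) | 22,024 (9.5%) |
| Plus Phase I limits, Phase I quotas | 1,958 | 948 | 1,010 (52%) | 364 (19%) |
| Plus scaled limits, Phase II quotas | 2,034 | 994 | 1,040 (51%) | 382 (19%) |

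The unrounded scaled limits accept 1,998, with the same percentages. The section 2.5.4 limits applied as written to the Phase II quotas accept none: they need a harmonic mean of 65 to 71, and the Phase II quotas target 182. The Phase II limits must be rewritten in any case.

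**Bias from imbalance.** With k former RDT clinics in Arm 3 and clinics weighted equally, bias = carry-over × (k − (11 − k)) / 11. Absolute values in percentage points:

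| Split | Carry-over 5 | 10 | 20 |
|---|---|---|---|
| 5:6 (section 2.5.6, rounded) | 0.5 | 0.9 | 1.8 |
| 4:7 | 1.4 | 2.7 | 5.5 |
| 3:8 | 2.3 | 4.5 | 9.1 |

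**Four strata (province × Phase I arm).** With 3:3 in each Nangarhar stratum and 2:3 and 3:2 mirrored in Kunduz, there are 2 × C(5,2) × C(5,3) × C(6,3)² = 2 × 10 × 10 × 400 = 80,000 allocations. Of these, 612 meet the rounded scaled limits (600 unrounded). An overall 5:6 rule alone is weaker: of the 994 accepted allocations that meet it, 994 − 612 = 382 (38%) are uneven within a province.

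**The case against.** The strongest reply is that the specific sentence governs the general one. Section 2.5.6 conditions on Phase I arm, so the two sections together mean the restricted method applied within each Phase I arm. That is a fair reading. A reader might infer that Phase II ignores Phase I arm, or that the split cannot be done at all; neither is supported. Rounding to 5:6 and 6:5 is routine, and the Phase 2 schematic, which is not visible in the text available, may give the counts. The 4:7 and 3:8 biases arise only if section 2.5.6 is overlooked, and they rest on assumed carry-over.

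It is also fair that more and better training is what Arm 3 consists of, so some of the retraining belongs to the effect being estimated. Section 2.8.4 already lists prior training history as a covariate and leaves detail to an analysis plan. What stands is that section 2.5.1 does not name Phase I arm, that its limits cannot be reused, and that section 2.5.2 itself regards later adjustment as a weaker remedy than restriction at the start.

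Two further inferences fail. One is that former control clinics in Arm 3 have only the extended RDT module: section 2.5.1 gives Arm 1 refresher training under the national community strategy, and section 3.3 ticks that training for Arm 1, possibly without the RDT part. The other is that the Phase II conclusion should rest on former control clinics alone. That halves the clinics. With intra-cluster correlation 0.5 and 182 patients per cluster (section 2.8.3), the design effect is 1 + 181 × 0.5 = 91.5. Normal-approximation power for 50% versus 70% then falls from about 28% with 22 clinics to about 16% with 11.

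**Conclusion.** The concern holds as a minor to moderate one. Sections 2.5.1 and 2.5.6 do not describe the same procedure, an exact half of 11 clinics does not exist, and the Phase I size limits admit no Phase II allocation. If section 2.5.6 is followed with rounding, the history imbalance is one clinic in 11. That shifts the Arm 3 effect by about 0.9 to 1.8 points at an assumed carry-over of 10 to 20 points, small against 20 planned. If the section 2.5.4 methods were run alone, a 4:7 or worse split would occur in about 41% of allocations, or about half with size restrictions. The latter is approximate because the 1598 does not reproduce.

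The mixture of two training comparisons is an interpretive limit on the pooled contrast more than a bias, since history is nearly balanced under section 2.5.6. It rests on reading the absence of planned refresher training as applying to clinics that stay in Arm 2.

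**What to change.** Before the Phase II allocation is drawn:

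- Make section 2.5.1 match section 2.5.6 by re-randomising within four strata, province by Phase I arm. Replace the percentages with counts: 3:3 in each Nangarhar stratum, and 3:2 and 2:3 mirrored in Kunduz, with chance deciding which Kunduz stratum takes which. Each Phase II arm keeps 11 clinics.
- Restate the total-size and harmonic-mean limits for the Phase II quotas, and reconcile the health-post counts used for the third limit.
- Adjust the Phase II comparison for Phase I arm.
- Keep the pooled contrast as the main result, and report the Arm 3 minus Arm 2 difference by Phase I arm as a secondary result of lower precision.

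The cost is protocol wording and one more condition in the existing enumeration; no extra patients are needed. The acceptable set shrinks from about 2,000 to about 600 allocations, so the validity matrix of section 2.5.5 should be recomputed for it. The estimates by Phase I arm rest on 11 clinics each and will be imprecise.
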